## Abstract

**Objective::**

The Integrating Prevention into Connect Care for Health (IPiC-Health) initiative embeds a Screening, Brief Intervention, and Referral (SBIR) approach for health promotion into routine inpatient and ambulatory care, facilitated by the province-wide, EPIC™-based, electronic clinical information system in Alberta. The SBIR approach supports patients in achieving behaviour change regarding tobacco and alcohol use and physical inactivity. This methodological article describes the research plan to evaluate the implementation and effectiveness of SBIR intervention.

**Methods::**

This effectiveness-implementation hybrid study includes a quasi-experimental design for quantitative assessment of SBIR implementation (adoption/coverage) and effectiveness (behaviour change and health service use) outcomes. Each participating site recruits control patients for 6 months, followed by 15 months intervention. Patients are followed up for 12 months after recruitment to assess effectiveness outcomes. Mixed methods are used to assess implementation uptake, process, and experience.

**Expected results and implications::**

Recruitment and data collection activities are ongoing in participating sites. This effectiveness-implementation research will strengthen evidence and implementation guidance to inform spread and scale up of the approach across Alberta’s hospitals and beyond. An electronic record of patient’s risk factors can improve patients’ care and population health by making these data readily available to support care decisions.

## Background

Making use of opportunities for health promotion and disease prevention when people seek healthcare is critical to increasing the impact of healthcare on population health. Only 10–20% of what makes people healthy is attributable to the treatment of illness, while 30% has to do with individuals’ health behaviours [1]. According to recent reports of the World Health Organization, 22.3% of the world’s population use tobacco, 27.5% of the adult population do not meet the recommended level of physical activity, and 42.6% of the population are current consumers of alcohol [2,3,4]. In Alberta, 18% of the population smoke cigarettes, 28% engage in greater than low risk levels of alcohol drinking, and 70% do not get enough physical activity, as defined by the Canadian guidelines for a healthy lifestyle [5]. Tobacco consumption, alcohol misuse, and physical inactivity are leading modifiable risk factors for preventable chronic diseases (e.g., cancer, cardiovascular disease, respiratory diseases) and poor outcomes (e.g., complications and increased healthcare use or costs) [6,7,8,9,10,11,12,13,14,15]. According to the Canadian Population Attributable Riskfor Cancer study, in 2015, 28% of new cancer cases diagnosed in Canada were attributable to tobacco use, 5% to drinking alcohol, and 9% to physical inactivity [5]. Together, the three risk factors account for approximately 20% of total healthcare expenditures [15]. Importantly, these risk factors are modifiable by raising awareness and encouraging behaviour change; these negative impacts could be prevented or reduced by supporting patients’ health behaviour change [15,16,17]. Of the estimated 40% of cancers that are preventable, the greatest proportion are attributable to modifiable risk factors, including tobacco and alcohol use and insufficient physical activity [14].

Although incorporating screening for behavioural health risk factors and promoting healthy behaviour change are important goals for primary care, there are also compelling reasons to incorporate health promoting interventions within hospital-based care. Hospital settings provide opportunities to support a large proportion of patients to modify their risk to prevent chronic diseases and improve treatment outcomes. Tobacco and alcohol use and physical inactivity are common (43%–90%) among patients attending hospitals [18,19]. Also, these risk factors are common among diverse subpopulations (e.g., some minority populations and socioeconomically disadvantaged people). These subpopulations, who often lack access to family physicians and primary care, are over-represented in the hospital settings. Healthcare providers are a trusted source of information about health risks, and patients who are currently experiencing ill health are more responsive to health advice for lifestyle behaviour change [20]. Significantly, a large proportion of total healthcare costs are driven by the costs of hospital care related to diseases associated with these factors [7]. Although general medicine guidelines recommend counselling on these risk factors as standard practice, it is not reliably integrated into hospital care routines.

The health promoting hospitals and health services (HPH) concept, developed by the World Health Organization over 30 years ago based on the principles of the WHO Ottawa Charter for Health Promotion, aims to reorient health services from a solely curative focus toward more holistic health care that includes health promotion [21]. In Alberta, Canada, our Cancer Prevention and Screening Innovation group has implemented several initiatives during the last 10 years to integrate screening, brief intervention, and referral (SBIR), pertaining to modifiable risk factors for cancer, as an approach for health promotion in hospital settings [22,23]. Our earlier health promotion pilots evaluated the implementation feasibility of SBIR using a paper-based guidance and documentation approach [22] However, these pilot initiatives as well as the existing global literature have lacked rigorous measurement of the health and healthcare impacts of this kind of HPH initiative as well as evidence-based guidance to support spread and scale out of implementation [24,25]. Research evidence on the effectiveness of HPH is limited, particularly in Canada, with no high quality peer reviewed studies yet published in English [24]. Most existing studies relied on surveys, interviews, and case studies to explore the enablers and barriers of HPHS projects. However, they offered limited evaluation of intervention implementation processes, impacts, mechanisms of impact, and contextual factors, and often lacked the use of appropriate study designs [24]. To enable large-scale integration of health promotion activities into routine hospital care, clinical leaders and decision makers need both good evidence of their effectiveness as well as evidence-informed implementation guidance pertinent to regular clinical settings. There is a clear need for more rigorous evaluation with focus on effectiveness and implementation outcomes and dissemination of results to inform the integration, spread, and sustainability of prevention-oriented hospital care.

The traditional research approach that focuses on testing an intervention under ideal conditions (i.e., efficacy and effectiveness trials) followed by real-world effectiveness trials before considering translation into regular clinical practice takes a significant amount of time and resources. The field of implementation science has offered a potential means to accelerate uptake of innovations, through the methodologies for effectiveness-implementation hybrid studies [26,27]. Hybrid studies can simultaneously incorporate formative (process and developmental) and summative evaluation methods, providing a comprehensive understanding of the real-world effectiveness of an intervention, the implementation process or strategies used to deliver it, and implementation outcomes [26,27]. Hybrid studies can offer more useful information for decision-makers, balance internal and external validities, and speed the translation of research findings into routine practice.

By early 2025, Alberta completed a multi-year province-wide roll out of a single EPIC™ electronic clinical information system (locally called “Connect Care”) in all of its hospitals, ambulatory care clinics, public health services, continuing care facilities, and laboratory services. This technology offers a sustainable opportunity to integrate, SBIR approach to health promotion within routine patient care workflows, guided by and documented in an electronic information system. The electronic capture of data related to routine care also makes evaluation of the implementation process and the downstream impacts on patient’s health and healthcare system far more feasible.

Our current initiative in Alberta, Canada – the Integrating Prevention into Connect Care for Health (IPiC-Health) project has two-fold objectives: (a) to integrate SBIR, to identify and address tobacco use, alcohol use, and insufficient physical activity, within Connect Care-facilitated patient care workflows in a variety of acute and ambulatory care settings, as a routine component of care; and (b) to demonstrate the feasibility and impacts, on patient outcomes and health system costs, of SBIR implementation within these settings. The IPiC-Health initiative intends to strengthen the quality and generalizability of effectiveness evidence and implementation guidance to inform spread and scale out of the approach to a wide variety of clinical programs. This methodological paper describes the research plan to rigorously evaluate the implementation and effectiveness outcomes of SBIR intervention.

## Overview of the Program

### Description of intervention and settings

The IPiC-Health initiative is a three year project (January 2023-December 2025) that engages a variety of ambulatory and inpatient healthcare sites and providers in delivering SBIR for health promotion as a routine component of patient care. These sites provide care to patients with a variety of acute and chronic health issues, including rheumatological conditions, surgery, diabetes, pneumonia, asthma, cardiac diseases, trauma, and geriatrics. This initiative leverages the province-wide electronic (“Connect Care”) clinical information system to help integrate the SBIR actions and documentation sustainably into routine care. Screening involves using standardized screening questions to identify patients who use commercial tobacco, consume alcohol at levels that increase risk, or who participate in insufficient physical activity [28,29,30,31,32,33]. The brief intervention is a conversation that providers have with patients who have elevated risk on one or more of those modifiable risk factors. The brief conversation aims to educate patients about the health risks, identify patient readiness to consider a change in behaviour, and to encourage them to take action. Providers are then able to offer educational resources (e.g., a brochure containing QR codes/links to relevant websites) that provide behaviour change information and support. Providers can also refer patients to support services available in their community (e.g., Alberta Quits program for tobacco cessation) (Figure 1).

**Figure 1 F1:**
[figure not shown]
SBIR workflow.

Connect Care contains evidence-informed, Alberta-relevant screening tools, risk algorithms, patient education materials, and referral information pertinent to tobacco use, alcohol misuse, and physical inactivity. We are working to optimize the use of these tools/resources by collaborating with the clinical teams, patients, and Connect Care experts to learn and demonstrate how Connect Care can facilitate practical delivery of SBIR for these risk factors within various clinical programs and workflows. We work with each clinical team to ensure that providers can confidently conduct brief educational/motivational conversations with patients using patient education materials and conversation guides/scripts developed/embedded within Connect Care. We identify health behaviour change support services available to patients in Alberta and within the local areas of the participating hospitals and ensure that information about them is accessible through Connect Care to provide patient information and referrals.

### Anticipated implementation challenges and strategies employed

Based on lessons learned from our previous SBIR pilots and our review of the global literature, we anticipated several factors that can hinder or help the implementation of SBIR in hospitals. These include: change fatigue and competing priorities, patients’ perceived or experienced stigma and providers’ discomfort to discuss behavioural risk factors with patients, functionality of the Connect Care system to support this work, limited capacity/motivation to provide preventive care in hospital settings, resources/support available to deliver SBIR or Connect Care support, and the adaptability of SBIR within a variety of clinical workflows [22,23,34,35]. Accordingly, several strategies (tools, training, technical assistance, and quality improvement methods) are planned and implemented together with stakeholders at each participating site to address the anticipated barriers and facilitate successful SBIR implementation and adaption [35,36]. The tools include a SBIR implementation guide, a single page information sheet (“cheat sheet”) to guide providers in delivering and documenting SBIR. Training of the clinical team members involves 1:1 or group in-person education and information sessions on how SBIR contributes to patient recovery and health (tailored to the specific patient populations/conditions served by each site), and how to complete and document SBIR using Connect Care. Technical assistance includes continuous engagement, by the research and implementation support team, with clinical team members and their leaders to build trust and to co-design the tailored support they need. Research staff are embedded in clinical sites to undertake the research activities of our project and to support clinical staff by offering regular coaching and troubleshooting concerning the delivery and documenting of SBIR. Quality improvement support involves continuous assessment of implementation, identifying “what worked’ or didn’t, and why, and provision of feedback reports on the clinical teams’ progress in implementing SBIR. We work proactively with clinical teams to refine the implementation strategies. The implementation sites and units were intentionally selected to ensure that no other major initiatives were occurring concurrently

Clinical teams were given flexibility to tailor the implementation process and the timing of brief intervention conversations to best align with patient needs and existing clinical workflows. In acute care settings, for example, these conversations were typically initiated during the later stages of hospitalization, such as in the days leading up to discharge, during discharge preparation, or once patients had passed the most acute phase of their stay. When clinical teams determined that the hospital setting was not appropriate for delivering the intervention to particular patients, providers were empowered to use their clinical judgment to assess the suitability of the intervention. In situations where hospitalized patients were not ready or able to engage with substantial information, patients were given the option to decline the intervention or to receive it during subsequent clinical encounters.

## Methods

### The design and key features of implementation and evaluation

We employ implementation-effectiveness hybrid study using mixed-methods [26]. This includes quasi-experimental design for quantitative assessment of SBIR implementation (adoption/coverage of intervention) and effectiveness (patient behaviour change and health service use) outcomes. We use both quantitative and qualitative methods to evaluate the implementation processes and providers’ experience of integrating SBIR into their workflows and patients’ experience of the SBIR intervention and of health behaviour change. Each participating site participates in a 6-month pre-implementation period, followed by 15-month SBIR implementation research period. Patients are followed up at 1, 6, and 12 months after they receive the SBIR intervention (Figure 2). Clinical sites that had used Connect Care for at least 6 months prior to recruitment into this project, and where the team identified health promotion and disease prevention as a priority, and expressed interest in participating in the study were engaged to participate.

**Figure 2 F2:**
[figure not shown]
Overview of Intervention Implementation Design.

During the 6-month pre-implementation period, our onsite research coordinators recruit a no-intervention (control/comparison) group of study participants and conduct risk factor screening on recruited patients using paper-based version of the same screening tools as those in Connect Care that will be used during SBIR implementation. These patients do not receive risk factor screening by clinical team members and are not offered brief intervention and referrals. The 15-month SBIR implementation serves as the intervention period of the study during which patients are recruited to participate in the intervention group. Note that all patients served by the participating clinics/units during the intervention period are *eligible* to receive the SBIR intervention, regardless of whether or not they agree to participate in the research study. Over the course of the 15 months intervention period, as the SBIR practice is increasingly embedded into routine care, we expect a growing proportion of the patients served by the participating clinical teams will receive SBIR. Enrolled research participants are followed up over the course of 12 months (1, only for intervention group, 6, and 12 months) for collection of behaviour change and health services utilization data. During the monitoring of participant recruitment, any control participants who had subsequent visits to intervention sites and received the intervention at that time were excluded from the study.

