### Research plans for evaluating implementation outcomes and process

*Study design and participants:* We use a quasi-experimental interrupted time-series design, covering a 6-month pre-implementation period and the last 12 months of the 15-month SBIR implementation period. The first three months of the implementation period are not used in analysis because we expect the quality of the SBIR intervention will mature over the first few months during which the clinical team learn to apply the practice.

*Definition and measurement of implementation outcomes*: Intervention reach (number) and patient population coverage (proportion) will be measured for each component of the SBIR intervention. Thus, the number of patients i) screened; ii) advised; and iii) referred in relation to each risk factor will be extracted each month from the Connect Care data. The denominator for the coverage (proportion) measures will be based on the total number of patients seen by a participating unit in the same month.

*Analysis:* For each outcome, we will calculate monthly summaries, aggregated across participating units. A Poisson regression model will be used to estimate the difference between the post-intervention observed rate and the “spontaneous” rate that would have occurred had SBIR been not implemented. The analysis will account for seasonality by decomposing the data in trend, seasonal, and random components, and then removing the seasonal component.

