**Pre-implementation Phase (6 Months Control Period)**				

Baseline, for comparison of SBIR (Screening Brief Intervention, and Referral) effectiveness	Tobacco consumption, alcohol intake, and physical activity levels	Proportion of patients with tobacco consumption, alcohol misuse, and insufficient physical activity levels	Primary data collection from comparison patient group	Paper-based self-administered questionnaire

Pre-implementation (baseline) delivery of SBIR elements by clinical team members.	Providers’ baseline delivery of SBIR elements to patients	Proportion of patients being screened, advised, and referred for each risk factor	Connect Care documentation (electronic health records)	Connect Care data extraction, monthly time points for six months

Baseline	SBIR implementation readiness	Leadership engagement/support, resources for SBIR, providers’ motivation	Primary data collection from providers and organizational leaders	Self-administered questionnaire, interview, and observation

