## Research plans for evaluation of intervention effectiveness outcomes

*Study design and participants:* We use a quasi-experimental study design (pre-post with a comparison group). The intervention group are patients from participating units during the SBIR implementation period who screen at increased risk on any of the three risk factors and received brief intervention and referral support. The comparison group are patients from the same units, during a 6-month pre-implementation period, identified as having increased risk on any of the three risk factors, but who do not receive the SBIR intervention.

Study inclusion criteria for the target patient population to be enrolled in the effectiveness study include: Adult patients (>18 years) who are residents of Alberta, have the ability to engage in the SBIR process and data collection, and are attending the participating sites during the study period. Research assistants enroll the eligible patients in the study after they provide informed consent. The patients with severe disease conditions (i.e., unconsciousness and end-stage care) or those with mental or cognitive incapacity are excluded.

*Outcome definition and measurement for both groups:* Key outcomes are patient behaviour change in relation to the modifiable risk factors and health care utilizations in the year after recruitment to the study. Measurement of patient’s behaviour changes involves: questions on patients’ intention to change behaviour, their uptake of referral services (for those who received referrals), and changes in risk level as measured using the same risk factor screening tools used during the SBIR intervention. We also ask patients about tobacco use reduction, tobacco quit attempts, seven- and 30-day tobacco abstinence. The data are being collected via telephone interviews at 6 months follow-up after the index clinic visit, or discharge from a hospital stay, during which the patient was recruited into the study. A sample of participating patients are also called at 1 month after their hospital/clinic visit to ask them about their experience of the SBIR intervention.

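### Enrolled controls, said to get no screening, advice or referral from the clinical team, stay in the denominator of the baseline delivery rate; applied as written, this would lower that baseline

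*Protocol article*

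**What the plan says.** In the Protocol article, the text after Figure 2 (Methods, The design and key features of implementation and evaluation) describes the six-month control period. Research coordinators enrol a no-intervention group and "conduct risk factor screening on recruited patients using paper-based version of the same screening tools as those in Connect Care". It continues: "These patients do not receive risk factor screening by clinical team members and are not offered brief intervention and referrals".

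The implementation analysis (Research plans for evaluating implementation outcomes and process) is an interrupted time series "covering a 6-month pre-implementation period and the last 12 months of the 15-month SBIR implementation period". Its numerators are monthly counts of patients screened, advised and "referred in relation to each risk factor will be extracted each month from the Connect Care data". For the denominator: "The denominator for the coverage (proportion) measures will be based on the total number of patients seen by a participating unit in the same month". A Poisson model then estimates the difference between the observed post-implementation rate and the spontaneous rate expected without SBIR (screening, brief intervention and referral).

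Table 1, Pre-implementation Phase, lists "Pre-implementation (baseline) delivery of SBIR elements by clinical team members" as a quantity to be measured from Connect Care in those six months.

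In the effectiveness evaluation, the comparison group are patients of the same units and period "identified as having increased risk on any of the three risk factors, but who do not receive the SBIR intervention".

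**The concern.** The control patients and the baseline delivery rate come from the same units in the same months. One section states flatly that enrolled controls get no screening, advice or referral from the team. Two other places treat team delivery in that period as an unknown rate to be estimated over all patients seen.

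Taken literally, enrolled controls count in the denominator and cannot enter the numerator. Their screening is done on paper by research staff, so it would not be expected to appear among the Connect Care counts of team delivery. The baseline would then partly reflect how the study handles its own participants, and the change credited to implementation would be too large.

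If the sentence only describes care before SBIR begins, some controls may still be screened or advised in the ordinary course. The flat statement would then be inaccurate, and the article does not say how such controls are treated in the effectiveness comparison.

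**Working it through.** The article gives no baseline rate, unit volume or expected implementation effect, so there is no figure of its own to reproduce. The check is algebra plus a range.

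**Inputs from the article**
- 2,015 control participants recruited so far, all at medium or high risk; 4 inpatient units and 4 ambulatory clinics, 3 of these 8 still in the control phase (Expected Results and Applicability).
- Control period of 6 months per site (Methods).
- Risk factor prevalence of 43% to 90% among hospital patients (Background).

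**Assumptions (not in the article)**: patients seen per unit-month; the spontaneous rate p; f and p constant over the six months.

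**Step 1. Controls per unit-month.** 2,015 / (8 × 6) = 42.0. This average is a lower bound, because three units have not finished their six months.

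**Step 2. Share f of patients seen who are enrolled controls**

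| Assumed patients per unit-month | f = 42 / volume |
|---|---|
| 800 | 0.05 |
| 400 | 0.10 |
| 200 | 0.21 |
| 100 | 0.42 |

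**Step 3. Screening, sentence applied as written.** Observed baseline = p(1−f). The difference is overstated by f×p and the ratio by 1/(1−f).

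| f | p = 0.02 | p = 0.10 | p = 0.30 | Ratio inflated by |
|---|---|---|---|---|
| 0.05 | 0.1 points | 0.5 points | 1.5 points | 1.05 |
| 0.20 | 0.4 points | 2 points | 6 points | 1.25 |
| 0.40 | 0.8 points | 4 points | 12 points | 1.67 |

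Example with assumed f = 0.20, p = 0.10 and post-implementation coverage 0.60: the observed baseline is 0.08, so the difference is 52 points instead of 50 and the ratio 7.5 instead of 6.0. If p = 0, the difference is unaffected.

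**Step 4. Advice and referral.** These go to at-risk patients, and every control is at risk. Let r be the at-risk share of patients seen and a the spontaneous advice rate among them. The true unit rate is r×a; the observed rate is (r−f)×a, that is, the true rate times (1−f/r). At f = 0.20 the ratio is inflated by 1.29 (r = 0.90), 1.40 (r = 0.70) or 1.87 (r = 0.43), against 1.25 for screening.

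**Step 5. Would dropping controls from the baseline repair it?** For screening, yes, if teams screen regardless of risk level: the remaining patients show p. For advice and referral, no. The remaining patients show a×(r−f)/(1−f) instead of a×r. With assumed r = 0.70:
- f = 0.20: 0.50/0.80 = 0.625a against 0.70a, about 11% too low.
- f = 0.40: 0.30/0.60 = 0.50a against 0.70a, about 29% too low.

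This shortfall arises under either reading of the sentence, because dropping controls selectively removes at-risk patients.

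**The case against.** The strongest reply is that the article never tells clinicians to withhold anything. The sentence can be read as describing the state of affairs before SBIR exists, and the Background says such counselling is not reliably part of hospital routine. The plan to extract baseline delivery from Connect Care also suggests that usual practice continues. This stands: a withholding rule is one reading, not an established fact. It does not remove the conflict, because under the usual-care reading the flat statement cannot be relied on for every control.

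Second, the size rests on assumptions, and the planned estimate is a difference, on which the bias is f×p and may be small. This also stands. A reader who assumes still smaller units might infer more than a twofold inflation. That needs over half of all patients seen to be enrolled at-risk controls. The article reports 175 research participants among 447 SBIR recipients (39%). If control enrolment among at-risk patients were similar (an assumption), f would be 0.39 × 0.43 = 0.17 to 0.39 × 0.90 = 0.35, giving a ratio inflation for screening of at most about 1.5.

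Third, a reader might infer that the effectiveness contrast becomes SBIR against nothing and so overstates benefit. The documents do not support that. The comparison group is defined by not receiving the SBIR intervention, which is the programme set out in the Overview, not by the absence of incidental advice. The exclusion after enrolment likewise concerns controls who received the intervention at later visits. What remains is that the status of controls given incidental advice or referral is not stated.

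Last, a condensed article leaves operational detail to fuller documents. That is fair for instructions to clinical teams. But this article itself states the denominator, the baseline months and the handling of controls, and as stated they do not fit together.

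**Conclusion.** The point holds conditionally. If the statement about controls is applied as written and the spontaneous rate is above zero, the baseline is observed as p(1−f). The before-after difference in screening is overstated by f×p, and advice and referral are distorted more in relative terms.

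The article gives some reason to expect p above zero: guidelines recommend this counselling, Connect Care already holds the tools, and sites were chosen for their interest in prevention. It gives no value for p and no unit volumes. Over the assumed ranges in the working, the overstatement for screening runs from 0.1 to 12 percentage points. It is nil if p is zero or if the sentence only describes usual care. An inflated implementation effect is therefore a possibility to be ruled out, not an established error.

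**What to change.** - Reconcile the text after Figure 2, the implementation analysis section and Table 1: state whether the sentence about controls describes usual care or a study rule for enrolled patients.
- In the implementation analysis, report the pre-implementation screening rate with and without enrolled controls.
- For advice and referral, do not simply drop controls. Extract the baseline also from Connect Care months before control recruitment began, and use it as the baseline or as a sensitivity analysis. The site criteria require at least 6 months of Connect Care use before recruitment into the project, so such months should exist.
- In the effectiveness section, state that controls with incidental usual-care advice or referral stay in the comparison group, and report their proportion.

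The cost is clarified wording and a little more data extraction, with possibly a less favourable contrast. The article says analysis awaits complete data, so this can still be settled beforehand.
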